### Adherence to the intervention

Adherence to the allocated intervention is defined as survivors having completed the thorough individual assessment of rehabilitation needs, having completed the neurocognitive assessment, and being informed of the individually tailored intervention plan, regardless of a potential drop-out from the intervention after these core intervention elements.

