### Intervention

Individuals allocated to the intervention group will in addition to the usual care group receive a comprehensive tailored rehabilitation intervention focusing on supporting RTW.

The intervention is based on a multidisciplinary rehabilitation team approach (psychologists, physiotherapists, social workers, physicians within social medicine and occupational medicine, and psychiatrists). A comprehensive neurocognitive assessment and a thorough individual assessment of rehabilitation needs will be conducted to inform the individually tailored intervention plan. The plan will be developed, discussed, and planned at multidisciplinary rehabilitation team conferences. Ongoing monthly evaluation and possible adjustments of the rehabilitation plan are further discussed at multidisciplinary rehabilitation team conferences. The intervention is designed as a pragmatic individually tailored rehabilitation intervention; hence, the content and the delivery of the rehabilitation will not be uniform but based on individual needs. Therefore, based on the individual rehabilitation plan, a participant can be offered interventions that target the individual needs without limitations in relation to frequency and intensity but with a limit in relation to duration (up until 12 months after the cardiac arrest). Core intervention elements are as follows: (1) comprehensive assessment of individual rehabilitation needs including neuropsychology tests in order to make an individually tailored intervention plan coordinated with the multidisciplinary rehabilitation team; (2) providing strategies to lessen impact for the individual cognitive impairment; (3) educating survivors and relatives about the impact of a cardiac arrest and consequences on daily life; (4) work preparation, including establishment of routines and opportunities to practice work skills; (5) collaboration with the local municipality’s job centre and employers to plan, support, and monitor graded RTW; and (6) short-term therapy by psychologist dealing with thoughts and behaviour in relation to cardiac arrest. Core elements and reference activities in the intervention related to timing are presented in Fig. 1.

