**Fig. 1 Fig1:**
[figure not shown]
Core elements and reference activities in the intervention. In addition to the usual care, the pragmatic individual tailored rehabilitation intervention can be delivered for up to 52 weeks

The complex pragmatic intervention is based on a multidisciplinary rehabilitation team approach and developed from a bio-psychosocial model perspective. The intervention is based on the principles from the individual placement and support [13] and stepped care [14] graded exercise therapy [15, 16] and cognitive behavioural therapy [17]. Individual placement and support is a model within rehabilitation focusing on RTW, where the goal is to provide professional services to help people with disabilities participate in the competitive labour market [18]. Stepped care is a system used to monitor and deliver the most effective treatment with the lease resources [14]. Graded exercise therapy is a behavioural treatment programme characterized by graded activity, time contingency, and operant conditioning. The primary aim of this rehabilitation programme is to increase the survivors’ ability to perform their own preferred activities during daily life at home or at work [15, 16]. Cognitive behavioural therapy is a short-term, goal-oriented psychotherapy treatment that takes a hands-on, practical approach to problem-solving [19].

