### Per protocol population

For survivors to be included in the per protocol analysis on the primary outcome, they should be classified as adherent to the intervention. Furthermore, to be included in the per protocol analysis for the secondary outcome, the first assessment timepoint and an assessment after 52 weeks are needed. No exclusion criteria will be imposed in relation to the usual care group.

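### Adherence is met once the plan has been explained, so it measures uptake of one of six core elements, and the per-protocol analysis built on it is a one-arm exclusion that does not test delivery

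*Protocol article*

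**What the plan says.** All places are in the protocol article.

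- **Intervention** lists six core elements. The first is a "comprehensive assessment of individual rehabilitation needs including neuropsychology tests in order to make an individually tailored intervention plan". The other five are strategies for cognitive impairment, education of survivors and relatives, "work preparation, including establishment of routines and opportunities to practice work skills", "collaboration with the local municipality’s job centre and employers to plan, support, and monitor graded RTW", and short-term psychological therapy. The caption of Fig. 1 says that "the pragmatic individual tailored rehabilitation intervention can be delivered for up to 52 weeks".
- **Adherence to the intervention** asks for a completed needs assessment, then "having completed the neurocognitive assessment, and being informed of the individually tailored intervention plan". It counts these participants as adherent "regardless of a potential drop-out from the intervention after these core intervention elements".
- **Per protocol population** says that, for the primary outcome, "they should be classified as adherent to the intervention". For the comparator it says: "No exclusion criteria will be imposed in relation to the usual care group".
- **Definition of analysis** describes the per-protocol population in another way, as survivors whose rehabilitation plan contains planned return-to-work interventions. It also plans intention-to-treat and complete-case analyses.
- **Adverse events** says that adherence will be registered. It names no measure of what, or how much, was delivered.

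**The concern.** A reader expects an adherence rate to say how far the intervention was delivered, and a per-protocol analysis to describe people who received it. Here the status is fixed at the start of a period that can last up to a year, and later departure does not alter it. The elements aimed most directly at work come after that point.

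Three things are at stake. First, if the trial finds no difference, the adherence rate will not help to separate an ineffective intervention from one that was planned but not delivered. Second, the per-protocol analysis selects on a post-randomisation event in one arm only, so it gives up the protection of randomisation without gaining a delivered-treatment population. Third, two different rules for the same population leave a choice open at analysis.

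**Working it through.** The protocol reports no adherence rate and no per-protocol sample size, so there is no figure of that kind to reproduce. The check compares the sections and then illustrates the size.

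**1. Adherence steps against core elements**

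| Core element (Intervention) | Needed for adherence? |
|---|---|
| (1) Assessment, neuropsychology tests, plan | Yes |
| (2) Strategies for cognitive impairment | No |
| (3) Education | No |
| (4) Work preparation | No |
| (5) Job centre and employers, graded return to work | No |
| (6) Short-term therapy | No |

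One of six elements is covered. Someone who leaves directly after hearing the plan is adherent.

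**2. The two per-protocol rules**

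| | Per protocol population | Definition of analysis |
|---|---|---|
| Intervention arm | Assessed and told the plan | Plan contains return-to-work interventions |
| Usual care arm | No one excluded | Not stated |
| Requires receipt after the plan? | No | No |

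The rules conflict. An assessed participant whose plan holds no return-to-work intervention is in under the first and out under the second. The second does not cure the problem, because it too rests on planning.

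**3. What the one-arm exclusion does**

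Let s be the share of the intervention arm that starts. Let p1S be the return-to-work rate of starters in the intervention arm, p0S the rate of their counterparts in usual care, and p0N the usual-care rate of those who would not have started. Usual care is kept whole, so

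per-protocol difference = p1S − [s × p0S + (1 − s) × p0N] = (p1S − p0S) + (1 − s) × (p0S − p0N).

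The second term is selection bias. It vanishes only if everyone starts or if starters and non-starters have the same prognosis. Its sign is unknown: non-starters could be the most impaired, or those already back at work.

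**4. Dilution, as an illustration**

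Inputs from Sample size: control rate 71%, and a 25% relative increase, 0.71 × 1.25 = 0.8875, which the protocol gives as 88.8%. The difference is 88.8 − 71 = 17.8 points. Let q be the share of adherent participants who leave after the plan and keep the control rate. q is an assumption; the protocol gives no such figure.

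Rate among the adherent = (1 − q) × 0.888 + q × 0.71, so the difference = (1 − q) × 17.8 points.

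| q | Rate | Difference (points) | Odds ratio |
|---|---|---|---|
| 0 | 88.8% | 17.8 | 3.24 |
| 10% | 87.0% | 16.0 | 2.74 |
| 20% | 85.2% | 14.2 | 2.36 |
| 30% | 83.5% | 12.5 | 2.06 |

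Every one of these participants counts as adherent in every row, so the adherence rate is the same throughout.

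**The case against.** The strongest defence is that the definition is deliberate. Under Intervention, content and delivery are tailored to need, and no element after the assessment and plan is stated as required for everyone. The adherence rule therefore measures the part common to all. Someone may stop because work has resumed, and a delivery threshold would label that success as non-adherence. A stricter one-arm exclusion would also worsen the selection shown in step 3. All of this stands. It argues against tightening the exclusion, but it does not make the present status a measure of delivery.

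Several stronger readings are tempting, and the documents do not support them:

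- *Adherent participants may have had no rehabilitation.* They have received element (1), and usual care, including municipal rehabilitation where referred, continues in both arms.
- *Per protocol merely repeats intention to treat.* Definition of analysis bases intention to treat on attendance at the first visit. Per protocol also drops intervention participants who did not finish both assessments or were not told the plan. The sets differ.
- *Reported adherence will be close to complete.* No figure for completion of the assessments is given, and Strategies to improve adherence names transport as a possible limit.
- *The 20% dropout in Sample size is the share leaving after the plan.* It inflates both arms, and Criteria for discontinuing the trial separates leaving the intervention from withdrawing consent.
- *17.8 points is the effect under full delivery.* It is the planning difference for the trial comparison. If it already allows for incomplete delivery, step 4 counts non-delivery twice.

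It is also fair to say that reporting of delivered dose could sit in the promised analysis plan, and that nothing in the adherence section forbids it. The definition of adherence and its use for per protocol are, however, already fixed in the protocol.

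**Conclusion.** The point holds as a matter of definition. The adherence status records uptake of core element (1) only and cannot show whether elements (2) to (6) were delivered. The per-protocol analysis of the primary outcome estimates the effect of having started, with a one-arm exclusion that can bias it in either direction. It has two conflicting definitions, neither of which requires receipt.

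The amount of dilution is unknown. The fall from 17.8 to between 16.0 and 12.5 points rests on three assumptions: that 10% to 30% of starters leave after the plan, that they gain nothing from the assessment and plan, and that 17.8 points applies to those who stay. It shows what the adherence rate would hide and is not a forecast.

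A reader might infer that the trial could not show whether the intervention works. That does not follow: intention-to-treat and complete-case analyses are also planned, and Superiority margins does not refer to per protocol. The consequence is for reading the result, above all a null one.

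**What to change.** 1. Rename the adherence status 'intervention started' and report it as uptake.
2. Report by participant which planned elements among (2) to (6) were delivered, marking those who stopped because they had returned to work. This is the step that exposes dilution.
3. Reconcile Per protocol population and Definition of analysis into one definition.
4. Replace the one-arm exclusion with a supportive complier analysis. Keep all randomised participants, use randomisation as the instrument and 'intervention started' as receipt. On the difference scale the estimate is the difference between the randomised arms divided by s. This equals p1S − p0S if allocation has no effect on people who do not start. That exclusion restriction is plausible with this receipt variable and should be stated as an assumption.
5. Do not use delivery of element (4) or (5) alone as receipt in that analysis. Elements (1), (2), (3) and (6) may themselves affect return to work, so the restriction would fail, and the effect would be overstated if they help.

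The cost is modest: wording in the analysis plan, which has yet to be uploaded before analysis, and one derived status. Delivery by element will need some extraction from team records. Monthly plan reviews and registration of adherence are described, but the protocol does not say that delivery is recorded by element. The complier estimate will have a wider interval, and the picture of delivery may look less favourable than the present adherence rate.

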### Per protocol population

For survivors to be included in the per protocol analysis on the primary outcome, they should be classified as adherent to the intervention. Furthermore, to be included in the per protocol analysis for the secondary outcome, the first assessment timepoint and an assessment after 52 weeks are needed. No exclusion criteria will be imposed in relation to the usual care group.

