### Secondary outcomes

All secondary outcomes: readiness for return-to-work (RRTW), Multidimensional Fatigue Inventory (MFI-20), The 5-level EuroQol 5-domain (EQ-5D-5L) quality-of-life questionnaire, European quality-of-life survey (HeartQoL), the Pittsburgh Sleep Quality Index (PSQI), Health Literacy Questionnaire (HLQ), and Impact of Event Scale-Revised (IES-R), modified job descriptions and job task, and adverse events will be collected within the first 12 weeks after hospital discharge. There will be at least one interim test at 26 weeks and again at the primary end point at 52 weeks. Please see assessment timeline in Table 1.

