#### Adverse events

During the trial period, serious adverse events, adverse events, and adherence will be registered. A serious adverse event is defined as an event that leads to either death, hospitalization, or a serious risk of deterioration in health, and all other reported adverse events such as pain, fatigue, and oedema are defined as non-serious adverse. Harms will be evaluated by calculating the relative risk (RR), separately for serious and nonserious adverse event between the intervention and control group.

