### Definition of analysis

Intention to treat, complete cases, and per protocol will be conducted for primary and secondary outcomes. Intention to treat is the sample of all survivors included who attended their first visit at the Center of Social Medicine. Complete case is the population with either a baseline assessment or assessment after 2 weeks and either a complete 6-month or 12-month assessment, for secondary end points to be derived. The per protocol population is the population of survivors with a rehabilitation plan including planned RTW interventions.

Sensitivity analysis will be conducted for the primary outcome on the following subgroups: blue collar vs. white collar, manual labour vs. non-manual, and doing several tasks at the same time vs. work concentrated on one issue at a time.

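### As written, the late-assessment rules for secondary outcomes also cover adverse events, so the complete-case set loses early deaths and the per-protocol set may lose deaths from the intervention arm only

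*Protocol article*

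**What the plan says.** All of this is in the protocol article.

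- *Secondary outcomes* (under Outcomes) puts adverse events in the same list as the questionnaires: "modified job descriptions and job task, and adverse events will be collected within the first 12 weeks after hospital discharge", with further collection at 26 and 52 weeks.
- *Adverse events* includes death in the definition: "A serious adverse event is defined as an event that leads to either death, hospitalization, or a serious risk of deterioration in health". The planned comparison is: "Harms will be evaluated by calculating the relative risk (RR), separately for serious and nonserious adverse event between the intervention and control group". The section names no analysis set.
- *Definition of analysis* states: "Intention to treat, complete cases, and per protocol will be conducted for primary and secondary outcomes". Adverse events are not exempted.
- The same section defines one of these sets: "Complete case is the population with either a baseline assessment or assessment after 2 weeks and either a complete 6-month or 12-month assessment". Its intention-to-treat set is limited to participants who attended a first visit at the Center of Social Medicine. Its per-protocol set is those with a rehabilitation plan that includes planned return-to-work interventions; no 52-week assessment is mentioned.
- *Per protocol population* gives another rule: "to be included in the per protocol analysis for the secondary outcome, the first assessment timepoint and an assessment after 52 weeks are needed". The next sentence says that the usual care group is subject to no exclusion criteria.

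**The concern.** Read together, these sections make entry to two of the three sets depend on an assessment that a participant who has died cannot supply. For a questionnaire score this is an ordinary, if imperfect, completeness rule. For adverse events it selects on the outcome being counted, because the participant is removed by the very event that the relative risk is meant to measure.

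The usual-care sentence makes this worse. If the 52-week rule acts on the intervention arm alone, fatal events leave one side of the comparison and stay on the other. An excess of serious events under the intervention could then appear as no difference, or as a benefit, in a prespecified analysis. The protocol defines no stopping guidelines and has internal data monitoring only, so the final harm comparison carries weight.

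**Working it through.** The plan gives no figure to reproduce. The check applies each definition to a participant who dies, then illustrates the size.

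**Step 1. Who stays in each set**

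| Set | Death before first visit | Death after first visit, before a complete 6-month assessment | Death after a complete 6-month assessment, before 52 weeks |
|---|---|---|---|
| Intention to treat | lost | kept | kept |
| Complete case | lost | lost | kept, given a baseline or 2-week assessment |
| Per protocol (*Per protocol population*), intervention arm | lost | lost | lost |
| Same, usual care, read literally | kept | kept | kept |
| Same, usual care, if the rule binds both arms | lost | lost | lost |

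Under the other per-protocol definition (*Definition of analysis*), no death is lost for want of a 52-week assessment; membership depends on having the rehabilitation plan.

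**Step 2. Illustration with unequal deaths**

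The 107 per arm comes from *Sample size*. Everything else is assumed: 8 deaths (intervention) v 3 (usual care), 25% of survivors hospitalised in each arm, and every survivor assessed at 52 weeks.

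- All randomised, intervention: 8 + 0.25 × 99 = 32.75 participants with a serious event. Usual care: 3 + 0.25 × 104 = 29. RR = (32.75/107)/(29/107) = 1.13. Fatal events: 8 v 3, RR = 2.67.
- 52-week rule in both arms: 0.25/0.25 = 1.00. Fatal events: 0 v 0.
- 52-week rule in the intervention arm only: 0.25/(29/107) = 0.25/0.271 = 0.92. Fatal events: 0 v 3.

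**Step 3. Range with equal mortality**

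The documents give no mortality after inclusion. Assume the same 12-month mortality d in both arms, from 2% to 10%, with 50% to 70% of deaths falling before the 6-month assessment. Expected deaths per arm are 107 × d. The complete-case set keeps 107 × d × (1 − early share). If the 52-week rule binds the intervention arm only, the RR for any serious event, again with 25% of survivors hospitalised, is 0.25/[d + 0.25 × (1 − d)]. The true RR is 1.00 throughout.

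| d | Deaths per arm, all randomised | Kept per arm, complete case | Per-protocol fatal events, intervention-only rule | Any-serious-event RR, intervention-only rule |
|---|---|---|---|---|
| 2% | 2.1 | 0.6 to 1.1 | 0 v 2.1 | 0.25/0.265 = 0.94 |
| 5% | 5.4 | 1.6 to 2.7 | 0 v 5.4 | 0.25/0.2875 = 0.87 |
| 10% | 10.7 | 3.2 to 5.4 | 0 v 10.7 | 0.25/0.325 = 0.77 |

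The direction does not depend on these assumptions. Everyone who dies has a serious event by definition, so removing the deaths from one arm lowers that arm's risk as long as some survivors have no serious event.

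**The case against.** The strongest reply is that harms have their own analysis. *Adverse events* says that events are registered throughout the trial period and compared by relative risk, with no attendance condition. That relative risk is not among the methods in the statistical section on secondary outcomes, and the completeness rules read as if written for repeated questionnaires. An unseen analysis plan may also name a safety population.

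Part of this stands. The link to harms runs through the list of secondary outcomes and the general sentence on analysis sets; the harms section does not make it. The absence of a named safety set would be no finding in a condensed article. But the article does state which sets apply to secondary outcomes, does place adverse events among those outcomes, and nowhere exempts them. The point is what the stated rules produce.

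A reader might also infer more than the text supports:

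- *That every harm analysis is confined to survivors.* Intention to treat keeps every death after the first visit.
- *That both restricted sets lose all deaths.* A complete 6-month assessment is enough for the complete-case set, so later deaths stay in.
- *That the per-protocol fatal comparison must be 0 v 0.* This requires the 52-week rule to bind usual care, which the next sentence speaks against, and requires that definition to prevail over the one in *Definition of analysis*.
- *That deaths would go unseen.* Safety data are reviewed monthly, and death is named as an end state in the multistate models.

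**Conclusion.** The concern holds in limited form. As written, the complete-case set drops deaths before a complete 6-month assessment. The set in *Per protocol population* drops deaths before the 52-week assessment, and on a literal reading does so in the intervention arm only, which favours the intervention. Under the assumptions of step 2, the relative risk for any serious event moves from 1.13 to 0.92 on that reading, or to 1.00 if the rule binds both arms. With equal mortality of 2% to 10%, a true 1.00 becomes 0.94 to 0.77. Death counts, mortality and the hospitalisation rate are assumptions, so only the direction is firm.

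Two further points follow. The two per-protocol definitions disagree, and the per-protocol consequence is undetermined until they are reconciled. Nor is intention to treat a full remedy: it loses any death between randomisation and the first visit, so none of the three sets is simply all randomised participants. This should be corrected before the analysis, but it concerns the restricted sets and does not make the trial's whole harms assessment unusable.

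**What to change.** 1. In *Adverse events*, state that serious and non-serious adverse events are compared in all randomised participants by allocated arm, with no visit or questionnaire requirement.
2. In *Per protocol population* and *Definition of analysis*, exempt adverse events from the complete-case and per-protocol rules for secondary outcomes.
3. Report deaths by arm as a separate line.
4. Reconcile the two per-protocol definitions, and say whether the 52-week requirement applies to usual care for the outcomes it still governs.

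The cost is a few sentences in the protocol or analysis plan, registered as an amendment as the article already provides. No new data are needed: adverse events are already registered during the trial period, and the DREAM register draws on the Civil Registration System.
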